### Intervention

The 'self help' self management materials will consist of an initial single 30-minute telephone support and education session with a nurse counsellor who will provide feedback to the participant about his/her levels of distress and instruction in evidence based strategies to improve adjustment. A self management manual will be developed purposefully for this study that will include self help in mood/stress management skills; problem solving approaches to cancer-related concerns; patient education about a healthy lifestyle to promote wellness and optimise quality of life; strategies for mobilising personal and community support networks to reduce isolation and seek sustainable social support. For the individualised cognitive behavioural intervention (therapist delivered), five weekly one-hour sessions of tele-based counselling from a clinical psychologist will be delivered that include psychoeducation, skills in stress reduction, problem-solving, cognitive challenging and enhancing relationship support. Cognitive behavioural approaches are well established with regards to their clinical efficacy for anxiety and depression in cancer and individualised approaches are more effective than groups [29]. The individualised counselling sessions will follow principles of cognitive-behavioural therapy and will utilise an adult learning approach in which participants self-select goals to focus on during the intervention. Content will include assigned behavioural homework that will be supported by work and tip sheets. Components that target challenges associated with cancer treatments (e.g., pain, sleep disturbance, fatigue) will be additionally selected if relevant. Minutes of counselling time will be recorded for inclusion in analyses for both arms.

### Participants

Study inclusion criteria will be that the patient/carer participants must: (1) be a cancer patient or carer ≥ 18 years of age who has called the Cancer Helpline for information or support (2) have a score of 4 or more on the Brief Distress Thermometer at the time of the Helpline contact (3) be able to read and speak English (4) have no previous history of head injury, dementia or psychiatric illness.

Callers who meet the selection criteria will be offered entry into the study by the Helpline operator at the time of the call; and once verbal permission to be contacted is obtained will be posted written consent and information forms. To minimise the period of time between calling the Helpline and randomisation into a support arm of the study, verbal consent to take part in the study will be obtained by project staff and audio taped prior to written consent. Baseline assessment will be conducted via telephone interview to prevent potential delays in receiving support. Participants will then be randomly allocated to receive either self management or the five session cognitive behavioural intervention. In all, 140 patients and 140 carers per condition will be recruited (allowing for a total of 280 people per treatment arm; 560 participants in total). On the basis of simulation work conducted by Raudenbush and Xiao-Feng [33], the present study, with 4 measurement periods and a total N of 560 will have power of at least .90 to detect a moderate longitudinal effect size. This sample size will allow for identification and investigation of subgroups of patients and carers (high vs. low/borderline distress) on the basis of their response to psychological intervention.

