## Methods/design

### Study aims and hypotheses

The overall aim of the proposed study is to compare the efficacy and cost effectiveness of minimal contact self management materials vs. a tele-based psychologist delivered cognitive behavioural intervention in improving psychological outcomes for high distress cancer patients and carers over a 12 month period. Callers who contact The Cancer Council Cancer Helpline in Queensland and New South Wales over a five month time period will be screened for psychosocial distress and those callers with *elevated distress *will be randomised to one of the two study arms. The two study arms will comprise: (1) minimal contact self management vs. (2) five sessions of an individualised tele-based cognitive behavioural intervention delivered by a clinical psychologist.

Study hypotheses: It is hypothesised that 3, 6, and 12 months after recruitment:

1. Participants in both study arms will experience significant improvements in mental health compared to baseline levels including: reduced anxiety and depression; cancer specific distress; unmet psychological supportive care needs; and increased positive adjustment and quality of life.

2. Participants with *borderline anxiety/depression *who receive the minimal contact self management condition will experience significantly less anxiety and depression; less cancer specific distress, lower unmet psychological supportive care needs, higher positive adjustment and improved quality of life **by comparison **to participants with *high anxiety/depression *who receive the minimal contact self management condition.

3. Participants with *high anxiety/depression *who receive the individualised tele-based cognitive behavioural intervention condition will experience significantly less anxiety and depression; less cancer specific distress, lower unmet psychological supportive care needs, higher positive adjustment and improved quality of life **by comparison **to participants with *high anxiety/depression *who receive the minimal contact self management condition.

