4. That from a health sector perspective, the individualised tele-based cognitive behavioural intervention is more 'cost-effective' compared to the minimal contact self management comparator for *high anxiety/depression participants*, **and **minimal contact self management is more cost-effective than the individualised tele-based cognitive behavioural intervention for *borderline anxiety/depression participants*; where $50,000 per QALY is taken as the benchmark for cost-effectiveness in Australia.

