### Study Integrity

Ethical approval has been obtained from the Griffith University Human research ethics Committee. The study design will be guided by the CONSORT statement [34]. Randomisation to study condition will occur following the completion of baseline assessment. Assessments will be by self-report pen and paper measures and project staff tracking assessments will be blinded to condition. Randomisation will be stratified by patient/carer and state (QLD vs NSW) and will occur in blocks of 10, with each condition randomly generated 5 times within each block to ensure an unpredictable allocation sequence with equal numbers of participants in each group at the completion of each block. This sequence will be undertaken by the project manager and concealed from investigators. Therapy will be manualised and all intervention calls audiotaped and reviewed to monitor treatment adherence. All analyses will be conducted on the basis of intention to treat.

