### Statistical Analyses

The study is a multivariate, two condition randomized controlled trial with repeated measures across time. The analytic approach will be a multilevel model (MLM) in which measurement occasions (level 1) are nested within persons (level 2) and in which state/program differences are represented as a fixed effect at level 2 whose interaction with time represents differential adjustment and distress trajectories for the two groups. A key advantage of this approach is flexibility in dealing with missing data owing either to random or non-random attrition. Further, subgroups of patients and carers who respond differentially to the program will be identified using growth mixture modelling that is a related longitudinal procedure that identifies cases with similar distress and adjustment trajectories across time [43]. Jo's [44] results suggest that the proposed sample size will be sufficient to examine subgroups of responders.

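### The Participants section ties the high and borderline groups to response after randomisation, whereas hypotheses 3 and 4 need groups fixed at baseline

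*Protocol article*

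**What the plan says.** All places are in the protocol article.

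- **Study aims and hypotheses.** Hypothesis 3 is an arm comparison inside the high anxiety/depression group: those "who receive the individualised tele-based cognitive behavioural intervention condition will experience significantly less anxiety and depression" than high-group participants given minimal contact. Hypothesis 4 compares cost-effectiveness inside each group. It favours the psychologist-delivered arm in the high group and claims that "minimal contact self management is more cost-effective than the individualised tele-based cognitive behavioural intervention for" the borderline group.
- **Background (Community-based approaches).** Borderline and clinical distress are described as the condition in which people come to care, and the question is which of them need more than minimal contact.
- **Participants.** The total of 560 is said to allow "identification and investigation of subgroups of patients and carers (high vs. low/borderline distress) on the basis of their response to psychological intervention". No other sentence says how the high and the low/borderline groups are identified.
- **Statistical Analyses.** After the multilevel model, "subgroups of patients and carers who respond differentially to the program will be identified using growth mixture modelling", a procedure that "identifies cases with similar distress and adjustment trajectories across time". The multilevel model is described with a program-by-time interaction; no term for baseline severity is named.
- **Study Integrity.** "Randomisation to study condition will occur following the completion of baseline assessment", and "Randomisation will be stratified by patient/carer and state (QLD vs NSW) and will occur in blocks of 10". Baseline severity is therefore known at allocation but is not a stratum.

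**The concern.** An arm comparison inside a subgroup is a randomised comparison only if membership could not have been affected by treatment. Baseline severity meets that condition; response does not. If high and borderline are assigned from data that include months 3, 6 and 12, a participant who improves under the psychologist-delivered intervention tends to leave the high group, while a similar participant in the comparison arm stays. The high group then keeps the less responsive part of one arm and sets it against a broader part of the other.

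The split is not a side issue. The Discussion presents the ability to look separately at high and borderline/low distress as a main advance of the trial, and hypothesis 4 carries the split into a cost-per-QALY conclusion about who should receive which service. An attenuated difference in the high group could lead to the conclusion that minimal contact is enough for people who do need more.

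**Working it through.** **1. The texts side by side.** The hypotheses and the Background fit a level held before treatment. The Participants sentence uses the same high versus low/borderline split but ties its identification to response, which exists only after randomisation. The one named subgroup method also uses follow-up data. So the article does more than leave out a cut-off: it states a rule that conflicts with what the hypotheses need.

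**2. The plan's own figure.** The stated power of at least .90 refers to the whole sample and to a moderate longitudinal effect. Effect size, alpha and variances are not given, so it cannot be reproduced exactly. It is plausible, taking two-sided alpha 0.05 as an assumption:
- Two means, 280 per arm: detectable difference = (1.960 + 1.282) × √(2/280) = 0.274 SD; power at 0.4 SD is 0.997.
- Linear slope, four equally spaced occasions: ncp = N × δ² × reliability / 4. With δ = 0.4 and reliability 0.5, ncp = 560 × 0.16 × 0.5 / 4 = 11.2, and power = Φ(√11.2 − 1.96) = Φ(1.387) = 0.917. At reliability 0.33 it is 0.78.

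This figure does not depend on how the subgroups are formed, so it neither supports nor weakens the point.

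**3. What grouping after randomisation does.** From the article: 280 per arm, one baseline and three follow-ups. Assumed: unit SD, within-person correlation 0.6, true high group = upper half at baseline, 1,500 simulated trials per row. Model: Y(baseline) = u + e; Y(follow-up) = u + e − d × arm, with var(u) = 0.6, var(e) = 0.4, and d depending on baseline group. Estimate = comparison mean minus intervention mean at the last visit inside the group labelled high (positive = benefit). The rejection rate at |z| > 1.96 is in brackets.

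| True d, high / borderline | Baseline split | Mean of follow-ups | Mean of all four | Two-cluster k-means | Change from baseline |
|---|---|---|---|---|---|
| 0.5 / 0 | 0.502 (0.997) | 0.184 (0.579) | 0.232 (0.766) | 0.227 (0.738) | 0.254 (0.603) |
| 0.5 / 0.2 | 0.506 (0.996) | 0.192 (0.607) | 0.252 (0.809) | 0.248 (0.793) | 0.336 (0.833) |
| 0.5 / 0.5 | 0.500 (0.995) | 0.183 (0.544) | 0.263 (0.821) | 0.256 (0.786) | 0.419 (0.923) |
| 0.5 / −0.3 | 0.501 (0.997) | 0.151 (0.423) | 0.183 (0.567) | 0.179 (0.535) | 0.081 (0.117) |
| 0.3 / 0 | 0.304 (0.825) | 0.121 (0.295) | 0.150 (0.405) | 0.150 (0.390) | 0.163 (0.291) |
| 0 / 0 | −0.007 (0.050) | −0.006 (0.050) | −0.007 (0.046) | −0.007 (0.045) | −0.006 (0.046) |
| 0 / 0.5 | 0.004 (0.050) | −0.050 (0.089) | −0.016 (0.049) | −0.019 (0.055) | 0.039 (0.061) |

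With a true 0.5 SD in the high group, grouping by follow-up level, all-occasion mean or k-means leaves 0.151 to 0.263, that is 0.151/0.5 = 30% to 0.263/0.5 = 53% of the effect. Grouping by change varies more, from 0.08 to 0.42. Part of the loss in the rows with unequal effects is dilution, because the relabelled group mixes in baseline-borderline people. The 0.5 / 0.5 row has no such dilution, so its loss comes from selection alone. The arms also become unequal in the high group: 158 versus 122 for follow-up grouping in the first row, against about 140 versus 140 at baseline.

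**4. A second set of assumptions.** With correlation 0.5 and a uniform effect of −0.40 SD (intervention minus comparison), the baseline-defined high half gives −0.40, and halves cut on the four-occasion mean give −0.21 each. Membership check: the arms differ in that mean by 3 × 0.40 / 4 = 0.30, its variance is 0.5 + 0.5/4 = 0.625, and Φ(0.15/0.791) ≈ 0.58. So 58% of the comparison arm and 42% of the intervention arm are labelled high.

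**5. Stratification.** The baseline split was not a stratum in the simulation of step 3, and its estimate is unbiased in every row. If half of the 560 are high, the number per arm has SD √(280 × 0.5 × 0.5 × 280/559) = 5.9, so the 95% range is 128 to 152 around 140. That affects balance only.

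**The case against.** The strongest reply is that a baseline definition was meant all along. The hypotheses speak of people with a given level who then receive an arm. The Background calls borderline and clinical distress prior states, and the Discussion wants effects compared across distress levels. Hypothesis 2 would be close to circular if groups were set by follow-up distress. The Participants sentence may be a loose way of saying that response will be compared between severity groups. Growth mixture modelling is introduced as an addition to the multilevel model and is never linked to the words high or borderline. A condensed article may also leave the scale and cut-off to a fuller document.

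Most of this stands. A reader might infer that the mixture classes are the groups in which hypotheses 3 and 4 will be tested; the article does not say so. The missing cut-off alone would be no finding. But if a baseline split was meant, the Participants sentence says something else, and it is the only text on how the groups are identified. It needs correcting on either reading.

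A reader might also infer that the arm comparison is compromised because severity is not a randomisation stratum. It is not: an unstratified baseline subgroup is still a randomised comparison. Stratifying by state is an ordinary choice for helplines managed by state.

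**Conclusion.** The point holds as a conflict in the text. Taken literally, the Participants sentence would set the high and borderline groups from post-randomisation data, and the comparisons of hypotheses 3 and 4 would no longer be protected by randomisation. When the high group truly benefits, as hypothesis 3 expects, the illustrative loss is about half of the effect or more for level- or trajectory-based grouping.

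These sizes rest on assumed correlations, an even split, and effects of 0.3 to 0.5 SD. Median splits and k-means only stand in for growth mixture classes, so the figures do not measure the planned analysis. A reader might conclude that the bias always runs towards no effect. That is too strong: there is none when treatment works in neither group; when only the borderline group benefits, the high-group estimate shifts slightly off zero (−0.05 to +0.04); and a mixture model with class independent of arm and class-specific arm effects need not attenuate.

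**What to change.** 1. Define high and borderline only from the BSI-18 anxiety and depression scores of the baseline interview, which is completed before randomisation, with the cut-off fixed in advance.
2. Test hypotheses 3 and 4 within these groups, with an arm-by-baseline-level-by-time term in the multilevel model.
3. Reword the Participants sentence so that the groups are not identified by response; say instead that response will be compared between baseline groups.
4. Label the growth mixture classes exploratory, and do not use them as the groups in which arms are compared.
5. Optionally, add baseline level as a randomisation stratum, for balance only. With state kept, this makes 2 × 2 × 2 = 8 strata and a few more incomplete blocks.

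Items 1 to 4 cost a little wording and analysis work and need no new data.

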### Study Integrity

Ethical approval has been obtained from the Griffith University Human research ethics Committee. The study design will be guided by the CONSORT statement [34]. Randomisation to study condition will occur following the completion of baseline assessment. Assessments will be by self-report pen and paper measures and project staff tracking assessments will be blinded to condition. Randomisation will be stratified by patient/carer and state (QLD vs NSW) and will occur in blocks of 10, with each condition randomly generated 5 times within each block to ensure an unpredictable allocation sequence with equal numbers of participants in each group at the completion of each block. This sequence will be undertaken by the project manager and concealed from investigators. Therapy will be manualised and all intervention calls audiotaped and reviewed to monitor treatment adherence. All analyses will be conducted on the basis of intention to treat.

### Measures

A computer assisted telephone interview will be undertaken for the baseline assessment; subsequent assessments will be administered by mail at 3, 6 and to 12 months after recruitment. A short telephone interview at follow-up time points will also re-assess participants' use of support services. Primary outcomes are anxiety and depression, cancer specific distress and unmet psychological supportive care needs. Secondary outcomes are positive adjustment and overall quality of life.

Background variables will include socio-demographic and disease variables (e.g. cancer site and stage, medical treatments received, use of alternative therapies) and previous (past month) and current use of support services.

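### Assessment mode switches from telephone to mail between baseline and month 3, so within-arm change from baseline (hypothesis 1) cannot be told apart from a mode shift; the arm comparison is unbiased but less precise than it could be

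*Protocol article*

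**What the plan says.** Two sections of the protocol article put the baseline on the telephone. Participants: "Baseline assessment will be conducted via telephone interview to prevent potential delays in receiving support". Measures: "A computer assisted telephone interview will be undertaken for the baseline assessment; subsequent assessments will be administered by mail", with the mailed assessments at 3, 6 and 12 months. A telephone call is also made at follow-up, but its described content is service use: "A short telephone interview at follow-up time points will also re-assess participants' use of support services".

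Study Integrity reads differently: "Assessments will be by self-report pen and paper measures and project staff tracking assessments will be blinded to condition". It makes no exception for baseline. The same section says "Randomisation to study condition will occur following the completion of baseline assessment".

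On analysis, hypothesis 1 expects improvement against baseline in both arms, and the hypotheses are set at fixed times: "It is hypothesised that 3, 6, and 12 months after recruitment". Statistical Analyses nests measurement occasions within persons and enters group as a person-level fixed effect "whose interaction with time represents differential adjustment and distress trajectories for the two groups". It then forms growth mixture classes on trajectories over time. The power statement under Participants counts four measurement periods, so baseline is one of the outcome occasions. The article does not mention a mode effect.

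**The concern.** People may answer questions about distress differently when an interviewer asks them than when they fill in a form alone. Here the switch falls at the same point for everyone, between baseline and the first follow-up. The follow-up call is not described as repeating any outcome scale, so nothing bridges the two modes.

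Three uses of the data depend on the step from baseline to month 3. Hypothesis 1 is that step or a longer version of it, and no between-arm difference is taken that could cancel a shift. The fitted trajectories contain it. So do the growth mixture classes, whose membership could be affected if the shift differs from person to person.

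A separate, milder point concerns the comparison between arms. If baseline is an outcome and the effect is a group-by-time interaction, the arm difference at a follow-up is in effect a difference in changes. That is less precise than a comparison adjusted for baseline.

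**Working it through.** **The plan's own figure.** 140 patients and 140 carers in each of two arms gives 140 × 2 × 2 = 560, as stated. The power of at least .90 cannot be reproduced, because the article gives no numerical effect size, significance level, variance components or attrition. It is compatible with the sample size: (1.960 + 1.282) × √(2/280) = 0.27 SD is detectable with .90 power in a simple two-group comparison (two-sided 5%, assumed). The statement matters here only because it counts baseline as the fourth occasion.

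**Inputs for the check.** From the article: 280 per arm, occasions at 0, 3, 6 and 12 months, baseline by telephone, the rest by mail. Assumed: unit SD at each occasion, correlation r between baseline and follow-up of .4 to .6, mode shift m of 0.1 or 0.2 SD, two-sided 5% test, no attrition.

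**Hypothesis 1, no true change.** The SE of mean change in one arm is √(2(1 − r)/280). The chance of a significant result from the shift alone is Φ(m/SE − 1.96) + Φ(−m/SE − 1.96).

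| r | SE | m = 0.1: m/SE, chance | m = 0.2: m/SE, chance |
|---|---|---|---|
| .4 | 0.065 | 1.53, 33% | 3.06, 86% |
| .5 | 0.060 | 1.67, 39% | 3.35, 92% |
| .6 | 0.053 | 1.87, 46–47% | 3.74, 96% |

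The nominal rate is 5%. The direction is unknown. If the telephone raises reported distress, the shift looks like improvement; if it lowers it, the shift hides improvement.

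**Between arms, single follow-up.** The variance of a difference in changes is 2 × 2(1 − r)/n. With baseline as covariate it is 2(1 − r²)/n. The ratio is (1 − r²)/(2(1 − r)) = (1 + r)/2, which is .70, .75 and .80 at r = .4, .5 and .6, whatever the sample size. At r = .5 and n = 280 per arm the SEs are √(2/280) = 0.085 and √(1.5/280) = 0.073.

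**Simulation.** 4,000 runs, 280 per arm, r = .5, assumed arm effect −0.30 SD at all follow-ups, no true change in the control arm, telephone lowering the baseline score. Results are for month 12.

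| Shift (SD between people) | Difference in changes (SE) | Baseline as covariate (SE) | Control-arm change, true value 0 | Same, baseline-adjusted |
|---|---|---|---|---|
| 0 (0) | −0.299 (0.083) | −0.300 (0.072) | −0.001 | −0.001 |
| 0.2 (0) | −0.296 (0.084) | −0.298 (0.074) | 0.199 | 0.200 |
| 0.2 (0.5) | −0.297 (0.094) | −0.299 (0.075) | 0.198 | 0.199 |

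The arm contrast stays at its true value under every shift. The within-arm change absorbs the whole shift, and adjusting for baseline does not remove it.

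**The case against.** The strongest reply is that the trial's main question is between arms, and that question is safe. This stands. Randomisation follows baseline, so both arms share the telephone mode and its expected effect cancels. A reader might infer that the mode change biases the randomised comparison; neither the documents nor the simulation supports that.

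Next, the Study Integrity sentence need not contradict the other sections. It follows the statement that randomisation comes after baseline, and it is joined to blinding, which has meaning only once people are allocated. Read as describing follow-up, it agrees with Measures. It also does not say that all assessments are on paper. This stands in part: the sentence is unqualified as written, and one clause would settle it.

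Third, hypothesis 1 was never a controlled comparison. Participants are selected on a distress score of 4 or more, and the Background says most people adjust over time without clinical intervention. This also stands. Mode is one further reason not to read the change as improvement, and the only one that is an artefact of measurement.

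Fourth, the telephone baseline was chosen deliberately so that support is not delayed. Nothing here asks for it to be dropped.

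Finally, a reader might take the group-by-time interaction to be a linear slope and object that it would miss an early or fading effect. The article does not say that time is linear. Hypotheses at three named times fit categorical time equally well, and the coding of time is commonly left to the analysis plan.

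**Conclusion.** The point holds, at moderate weight. Baseline mode and follow-up mode differ for everyone, so mode is fully aliased with the step from baseline to month 3. Hypothesis 1 and the shape of the trajectories cannot be separated from it. The aliasing follows from the design; its size is not in the documents. With an assumed shift of 0.1 to 0.2 SD, the false-positive rate for change within one arm is about 33% to 96% (280 per arm, r = .4 to .6, no attrition). Attrition would enlarge the SE and lower these rates somewhat.

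The comparison between arms is unbiased. It gives up precision if the arm difference at baseline is left free, as a group effect plus its interaction with time implies: the adjusted contrast has 70% to 80% of the variance. If the full analysis plan already constrains the baseline means to be equal, this part falls away.

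For the growth mixture models, a uniform shift moves every trajectory alike. Class membership is affected only if the shift varies between people, which the documents neither state nor exclude.

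It would be wrong to conclude that a baseline covariate cures the mode problem. It improves the arm comparison and leaves hypothesis 1 as it was.

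**What to change.** 1. Reconcile the Study Integrity sentence with Participants and Measures, for example by limiting pen and paper to the 3, 6 and 12 month assessments. Cost: one clause.
2. Estimate arm differences at each of the mailed 3, 6 and 12 month occasions, with the telephone baseline as a covariate, or keep baseline in the model with a common mean across arms. Cost: analysis wording only. Every randomised participant should have a baseline, since randomisation follows its completion.
3. Report hypothesis 1 change from baseline as descriptive, say that it crosses a change of mode, and make no claim of improvement from it alone. Cost: hypothesis 1 loses its standing as a test. The alternative of collecting both modes at baseline in a subsample would add data collection.
4. State that the growth mixture trajectories cross a mode change and that class membership may be affected if the shift varies between people. Restricting these models to the mailed occasions is possible, but it would drop the only pre-treatment point, so disclosure is the cheaper choice.
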